**Fig. 2 Fig2:**
[figure not shown]
SPIRIT Schedule of enrolment and interventions for the protocol. Note. t1–3 months after treatment start, t2–6 months, t3–9 months, t4–12 months (post-assessment), t5–6 months follow-up, t6–12 months follow-up

**Table 1 Tab1:** Assessments instruments and assessment times planned for the study. A detailed description of each instrument can be found in Supplementary Material 1: Appendix 2

Domain	Construct	Measure	Format	Acronym	Pre	0	3	6	9	12	18	24
Diagnostic Measures	BPD diagnosis	International Personality Disorder Exam (BPD subsection) [45]	Interview	IPDE	●						●	
	Comorbidities	Mini International Neuropsychiatric Interview DSM-5 [46]	Interview	MINI	●							
	Premorbid Functioning	Test of Premorbid Functioning [47, 48]	Interview	TOPF	●							
	ADHD	Adult ADHD Self-Report Scale [51]	Self-Report	ASRS	●							
	Personality Dimensions	Personality Inventory for DSM-5 [52, 53]	Self-Report	PID-5	●							
	Demographics	Demographic Data Survey	Self-Report	DDS	●							
Trauma Biography	Childhood Invalidation	Invalidating Childhood Environment Scale [54]	Self-Report	ICES	●							
	Childhood Trauma	Childhood Trauma Questionnaire [55]	Self-Report	CTQ	●							
	Complex Trauma	International Trauma Questionnaire [56]	Self-Report	ITQ	●							
	Embitterment	Posttraumatic Embitterment Disorder Questionnaire/Berner Embitterness Scale [57]	Self-Report	PTED/BEI	●							
	Unpredictability Childhood	Questionnaire of Unpredictability in Childhood [58]	Self-Report	QUIC	●							
	Bullying	Bullying Scale for Adults [59]	Self-Report	BSA	●							
BPD-related Psychopathology	BPD Symptoms	Borderline Symptom Liste - Interview	Interview	BSL-I		●	●	●	●	●	●	●
	BPD Symptoms	Borderline Symptom List 23 [60]	Self-Report	BSL-23	●	●	●	●	●	●	●	●
	Suicide Severity	Columbia Suicide Severity Scale [61]	Interview	C-SSRS		●	●	●	●	●	●	●
	Self-Harm	Deliberate Self-Harm Inventory [62, 63]	Self-Report	DSHI		●	●	●	●	●	●	●
	Emotion Regulation Difficulties	The Difficulties in Emotion Regulation Scale– 16 Item Version [64]	Self-Report	DERS-16		●	●	●	●	●	●	●
	Dissociation	Dissociative Symptoms Scale [65]	Self-Report	DSS		●	●	●	●	●	●	●
	Complex Trauma	International Trauma Questionnaire [56]	Self-Report	ITQ		●	●	●	●	●	●	●
General Psychopathology	General Psychiatric Symptom Distress	Symptoms Checklist 27 [66]	Self-Report	SCL-27		●	●	●	●	●	●	●
	Affective Suicidality	Acute Suicidal Affective Disturbance Interview [67]	Interview	ASAD-I		●	●	●	●	●	●	●
	Affective Suicidality	Acute Suicidal Affective Disturbance Questionnaire [67]	Self-Report	ASADI-L		●	●	●	●	●	●	●
	Severity Personality Disorder	Level of Personality Functioning Scale - Brief Form 2.0 [52]	Self-Report	LPFS-BF 2.0		●		●		●	●	●
Social Relationships and Affiliation	Loneliness	UCLA Loneliness Scale [68]	Self-Report	UCLA		●		●		●	●	●
	Social Connectedness	Social Connectedness Scale– Revised [69]	Self-Report	SCS-R		●		●		●	●	●
	Rejection Sensitivity	Rejection Sensitivity Questionnaire [70]	Self-Report	RSQ		●		●		●	●	●
	Need to Belong	Need to Belong Scale [71]	Self-Report	NBS		●		●		●	●	●
	Social Network Index	Social Network Index (+ Interpersonal Distance & Trust) [72]	Self-Report	SNI		●		●		●	●	●
Self-image and Self-esteem	Fear of Compassion	Fears of Compassion Scale [73, 74]	Self-Report	FCS		●		●		●	●	●
	Self-Esteem	Rosenberg Self-Esteem Scale [75]	Self-Report	RSES		●		●		●	●	●
	Self-Compassion	Self-Compassion Scale [76]	Self-Report	SCS		●		●		●	●	●
	Shame	Test of Self-Conscious Affect-3 [77]	Self-Report	TOSCA-3		●		●		●	●	●
	Aspects of Identity	Aspects of Identity Questionnaire [78, 79]	Self-Report	AIQ		●		●		●	●	●
Quality of Life and Wellbeing Outcomes	Functioning	Global Assessment of Functioning (Observation-Based) [80]	Interview	GAF		●	●	●	●	●	●	●
	Quality of Life	Recovering Quality of Life [81, 82]	Self-Report	ReQoL		●	●	●	●	●	●	●
	Psychosocial Functioning	Inventory of Psychosocial Functioning [83]	Self-Report	IPF		●		●		●	●	●
	Functioning– Social, Interpersonal, Global	WHO Disability Assessment Schedule 2.0–12-Item Version [84]	Self-Report	WHODAS 2.0–12		●		●		●	●	●
	Life Satisfaction	Quality of Life Enjoyment and Satisfaction Questionnaire– Short Form [85]	Self-Report	Q-LES-Q-SF		●		●		●	●	●
	Meaning of Life	Meaning of Life Questionnaire [86]	Self-Report	MLQ		●		●		●	●	●
	Mindfulness	Kentucky Inventory of Mindfulness Skills [87]	Self-Report	KIMS		●		●		●	●	●
Therapeutic Relationship and Acceptance Measures	Therapeutic Alliance	Working Alliance Inventory - Short Form, Client and Therapist [88]	Self-Report	WAI-S		● (S1-4)	●	●	●			
	Group Climate	Group Climate Questionnaire [89]	Self-Report	GCQ		● (S1-4)	●	●	●			
	Therapist Demographics	Therapist Demographic Questionnaire	Self-Report	TherDem		●						
	Acceptability of Intervention	Acceptability of Intervention Measure [90, 91]	Self-Report	AIM			●	●		●		
	Client Satisfaction	Client Satisfaction Questionnaire– 8 [92]	Self-Report	CSQ-8			●	●		●		
	Telehealth Usability	Acceptance and Use of Technology [93]	Self-Report	UTAUT			●	●		●		
Treatment Termination Measures	Reason for Treatment Termination	Research Early Termination for the Client*	Self-Report	RET-C								

Note: S1-S4 indicates that instruments are assessed in the first four session of individual therapy (WAI) and group therapy (GCQ)

*The RETC will be administered only if clients discontinue treatment prematurely

As compensation guidelines for participants differ in Canada and Germany, each site followed its own ethical standards of practice. At the German sites, participants did not receive financial compensation for data assessments while undergoing treatment. However, in cases where participants discontinue treatment prematurely but continue participating in research they receive €20 (US $21) for each subsequent assessment time point. At the Toronto site, all participants received CAD $15 (US $10.50) per assessment hour.

#### Primary outcome

*The Borderline Symptom List Interview (BSL-I*) was selected as the primary outcome of this trial, capturing the severity of BPD symptoms. The interview consists of 25 items assessing frequency (0 = never; 4 = very often) and associated distress (0 = no distress; 4 = most severe distress). Of these 25 items, four items additionally assess the consequences of behavioral symptoms (0 = no problematic behavior; 4 = behavior with extremely serious or life-threatening consequences). One additional item assesses psychosocial functioning in daily life (everyday life coping, social relationships, occupation,) and five items assess aspects of positive mental health. The BSL-I demonstrates good internal consistency within BPD samples (Cronbach’s α = 0.82), good interrater agreement (Kα = 0.76), as well as good criterion validity with high correlations with other established BPD self-report measures, like the BSL-23 (*r* = 0.83).

#### Secondary outcomes and potential mechanisms

As secondary outcomes, we will assess a broad range of outcomes and therapy processes, including (1) developmental relational trauma experiences (2), BPD-related psychopathology (3), general psychopathology (4), social relationships and affiliation (5), self-image and self-esteem (6), quality of life and wellbeing outcomes, as well as (7) therapeutic relationship and satisfaction with the intervention. The instruments used are depicted in Table 1, and a detailed description of each instrument can be found in Supplementary Material 1: Appendix 2.

In the present study, we primarily rely on the self-report and observer-based measures outlined above to assess change in BPD symptomatology and relevant domains. While validated psychometric instruments are considered the gold standard for assessing outcomes in intervention studies, they also provide a limited understanding of the psychological processes underlying change and may overlook treatment effects that manifest in clients’ daily lives. To expand the scope of this study, we aim to incorporate additional methods to capture clinical improvements and mechanisms of change beyond psychometric instruments. Specifically, we will employ experimental laboratory assessments of social information processing to directly evaluate potential psychological mechanisms of change and a prediction of treatment efficacy. Additionally, we will use ambulatory assessment methods to measure clinical outcomes and mechanisms of change in real-life settings. Experimental paradigms and Ambulatory Assessment procedures will be conducted at baseline, 2 to 4 weeks prior to the start of therapy, and at post-intervention, 2 to 4 weeks after the end of the intervention (12 months). Finally, to understand which psychopathological symptom clusters change in which phase of the treatment we will examine diary card data. This data is collected daily during treatment.

##### Experimental task battery 

Many experimental studies have identified alterations in social information processing (SIP) in BPD with the aim to understand impaired social functioning in these individuals. Alterations comprise self- and interpersonal functioning including cognitions, emotions and behaviours (e.g., [94–96]. However, studies are sparse that actually link these alterations in SIP to social functioning in BPD, to changes in the level of psychopathology after psychosocial interventions or to the stability of remission and recovery. Therefore, SIP and its changes after therapy will be assessed together with the participants’ appraisal of their social network as secondary outcomes using an experimental social-cognitive task battery and an egocentric social network survey. The central constructs of the task battery being assessed are social attitudes (value orientation), evaluation processes of social cues (attribution of emotions and trustworthiness to facial stimuli), inferring social causality (assessment of the likelihood of attributions in social scenarios), the experience of interpersonal closeness after simulated social interactions (partial cyberball paradigm with trust game) as well as the cognitive and emotional reactions to processes of self-evaluation. For a more detailed description, see Supplementary Material 1: Appendix 3.

##### Ambulatory assessment

The method of ambulatory assessments (AA) will be included to investigate emotional processing in clients’ daily lives. AA offers the possibility of repeated real-time assessments in patients’ natural habitat and, thus, the key advantages of examining dynamic processes with high ecological validity. AA data is used to examine disorder-relevant phenomena such as affect dynamics or stress reactivity [97, 98]. We hypothesize that individuals meeting the criteria for BPD, amongst others, suffer from intermittent implicit activations of cognitive-emotional networks, which deeply affect their day-to-day mental state. These maladaptive mental networks can be triggered by a variety of internal or external triggers or may result from dysfunctional social perceptions. We assume that the components of these maladaptive networks (cognitions, emotions, action tendencies, physiology) are highly individualized and closely linked. We further assume that activated maladaptive networks have an influence on implicit social evaluation processes. We aim to investigate whether TF-DBT, which specifically addresses these maladaptive networks, will reduce frequency and intensity of these networks in daily life circumstances. The AA protocol involves 4 days with 13 prompts per day assessing momentary cognitions, emotions, action tendencies and physiology and will be administered pre- and post-intervention. A more detailed outline of the procedure and materials can be found in Supplementary Material 1: Appendix 4.

##### Electronic diary card

The DBT diary card is an important therapeutic tool to promote patients’ self-reflection and to inform the therapist about the course of important symptoms (e.g., suicidal ideation, self-harm). In the past, this diary card has mainly been filled in paper-pencil to inform treatment processes and decisions. However, emerging research has demonstrated the utility of these data for research purposes (e.g., [99, 100]). Thus, in this study, we will administer the DBT Diary Cards electronically to use these daily data also for research purposes and to integrate them more easily into the online intervention. With this diary-card data, we aim to investigate the prediction of treatment response as well as premature therapy termination using machine learning algorithms [101, 102]. Furthermore, we aim to understand which symptom clusters change when during treatment, hypothesizing that dissociative symptoms, high suicidal urges, and behavioral dyscontrol change earlier in treatment, whereas improvements in maladaptive self-concepts, such as self-compassion, change later in treatment. The diary card will be administered on a daily level during the 12 months of treatment. A detailed description of the procedure and items used is outlined in Supplementary Material 1: Appendix 5.

### Statistical methods

#### Power analysis

The total sample size estimation of *N* = 260 is based on statistical power analyses regarding the intent-to-treat (ITT) sample. In comparing the treatment conditions (TF- DBT vs. S-DBT), a power of 1-*β* = 0.90 is aimed for detecting a minimum clinically relevant difference between the treatment conditions of *d* = 0.43, as recommended in the current Cochrane Review [10]. When comparing the treatment formats (online vs. face-to-face), an equivalence test with a power of 1-*β* = 0.90 is aimed for. The minimum relevant difference is also set at a standardized mean difference (Cohen’s *d*) of 0.43 in accordance with the current Cochrane review and the current Cochrane guidelines [10]. To achieve power, at least *n* = 230 participants are required. Because the psychotherapies investigated each require closed skills groups, participants are randomized into groups of 10. This results in a target number of cases of *N* = 260.

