### Improving access to care: evaluating online vs. face-to-face treatment delivery

There are barriers that limit access to DBT. As a specialized treatment, DBT is often available only at specialized centers in urban areas, making it difficult for many clients to access it [32, 33]. This issue is even more pronounced in developing and low- to middle-income countries [34]. Advancements in modern information technology have transformed the way psychotherapy can be delivered, leading to increased interest in the feasibility and effectiveness of internet-based and telehealth psychotherapeutic treatments as a means to improve access [35]. The COVID-19 pandemic further accelerated this shift, with DBT practitioners worldwide transitioning to telehealth delivery. Many clinicians in both healthcare centers and private practice now offer DBT remotely [36–38].

Despite this progress, concerns remain regarding the efficacy, safety, and feasibility of telehealth-delivered psychotherapy, particularly for patients with high levels of emotional and behavioral dysregulation [37, 39, 40]. There is limited empirical evidence comparing online psychotherapy to traditional face-to-face treatment, particularly in the context of DBT [41]. However, studies on other psychotherapeutic approaches—primarily cognitive behavioral therapy (CBT) for anxiety and affective disorders—have found no significant differences between online and face-to-face treatment formats [42, 43]. Preliminary findings from a feasibility trial to assess the feasibility, safety, and potential efficacy of online-delivered DBT in a controlled research setting are promising [44]. A total of 39 clients participated in one year of outpatient S-DBT treatment delivered online. Results indicated substantial pre-post effect sizes for BPD symptoms (*d* = 1.13 in the intent-to-treat sample (ITT) to 1.44 in the completer sample (ATP)) and quality of life (*d* = 0.65 in the ITT to 1.24 in the ATP). While the telehealth format was feasible and well-accepted, a relatively high dropout rate of 39% was observed. However, these results have not been compared to a face-to-face DBT group. Therefore, the present study includes a randomized comparison of online and face-to-face DBT across both treatments.

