#### Statistical analyses

The analyses of the clinical efficacy of the treatments are carried out by modeling the primary outcome using mixed linear models (MLM). To compare the efficacy of the two groups, the interaction between treatment condition (TF-DBT vs. S-DBT) or treatment format (online vs. face-to-face) and time is tested for significance. To estimate the effect sizes, standardized mean differences (Cohen’s d) are calculated in TF-DBT before and after therapy as well as between the groups (TF-DBT vs. S-DBT) after therapy.

The main analyses include the evaluation of the ITT sample, which includes all patients who were randomized to a treatment in the study (randomized is analyzed). To analyze the ITT sample, including all participants who had been randomized to the treatment, we will impute missing data by multiple imputation procedures [103]. In addition, the main analyses are performed for all patients who complete the therapy (according to protocol).

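### The required 230 assumes every outcome is observed, groups of 10 do not lead from 230 to 260, and the format comparison randomises only 220

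*Protocol article*

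**What the plan says.** All of the following is in the protocol article.

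- **Power analysis.** The sample size "is based on statistical power analyses regarding the intent-to-treat (ITT) sample". For TF-DBT versus S-DBT, "a power of 1-*β* = 0.90 is aimed for detecting a minimum clinically relevant difference between the treatment conditions of *d* = 0.43". For online versus face-to-face, "an equivalence test with a power of 1-*β* = 0.90 is aimed for", and the margin is the same: "The minimum relevant difference is also set at a standardized mean difference" of 0.43. At least 230 participants are said to be needed. The only reason given for going higher is that closed skills groups require randomisation in groups of 10. The section then states: "This results in a target number of cases of" 260. It gives no alpha and no rate of missing outcomes.
- **Trial design & hypotheses.** The quotas are 40, 40, 40, 20 and 80 at five locations, plus 40 German participants who live far from a site. The 40 distant participants are randomised between therapies but all treated online, so 220 are randomised between formats.
- **Improving access to care.** In the cited online S-DBT feasibility trial of 39 clients, "a relatively high dropout rate of 39% was observed".
- **Statistical analyses.** The primary outcome is analysed with mixed linear models, in which the group-by-time interaction "is tested for significance". For the ITT sample, "we will impute missing data by multiple imputation procedures".

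**The concern.** The section gives one power figure, one required N and one reason for the target, and three things do not fit. First, 230 looks like the plain two-sample answer for fully observed data, although the article elsewhere expects dropout and plans imputation. Including all randomised patients and imputing keeps the ITT principle, but it does not supply the information in an unobserved 12-month BSL-I. Second, 230 is a multiple of 10, so grouping by 10 gives no reason to add 30. Third, the stated requirement of 230 serves both comparisons, but the randomised format comparison has 220.

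At stake is how the results will be read. A null superiority result, or a failure to show equivalence of formats, would be judged against a stated 0.90. For the format comparison, the stated inputs do not deliver that figure even with complete data.

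**Working it through.** **Inputs.** From the article: d = 0.43 for both comparisons, power 0.90, required N 230, group size 10, target 260, 220 randomised between formats. Assumed, because not stated: two-sided alpha 0.05 for superiority, two one-sided tests at 0.05 with true difference 0 for equivalence, 1:1 allocation, standardised SD of 1, no clustering.

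**1. Reproducing 230.** Superiority, normal approximation: n per arm = 2 × ((1.960 + 1.282) / 0.43)² = 113.7, so 114 per arm and 228 in total. The t-test version gives 114.6, so 115 per arm and 230 in total, with power 0.901. The stated figure is reproduced with no attrition factor. Equivalence: n per arm = 2 × ((1.645 + 1.645) / 0.43)² = 117.1, so 118 per arm and 236 in total. At 230, equivalence power is 0.892.

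**2. From 230 to 260.** 230 / 10 = 23 whole groups. Rounding up to a multiple of 20 (two arms) or 40 (four cells) gives 240 in both cases. None gives 260. The site quotas do: 40 + 40 + 40 + 20 + 80 + 40 = 260.

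**3. What the extra 30 cover.** 1 − 230/260 = 11.5%. With 11.5% of 260 outcomes missing, 230 remain and superiority power is 0.901.

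**4. Power by share of missing 12-month outcomes, m.** Unadjusted figures use 130 × (1 − m) per arm for the treatment comparison (t-test) and 110 × (1 − m) for the format comparison (two one-sided tests at 0.05). Adjusted figures multiply the variance by 1 − r² = 0.75, for an assumed baseline correlation r = 0.5.

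| m | Treatment, unadjusted | Treatment, r = 0.5 | Format, unadjusted | Format, r = 0.5 |
|---|---|---|---|---|
| 0% | 0.932 | 0.979 | 0.876 | 0.958 |
| 10% | 0.906 | 0.966 | 0.830 | 0.934 |
| 20% | 0.870 | 0.946 | 0.769 | 0.899 |
| 30% | 0.823 | 0.915 | 0.689 | 0.846 |
| 39% | 0.768 | 0.874 | 0.596 | 0.777 |

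Example, format comparison with complete data: SE = √(2/110) = 0.1348; 0.43 / 0.1348 = 3.189; the critical t on 218 df is 1.652; power = 2Φ(3.189 − 1.652) − 1 = 0.876.

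**5. Dependence on the test.** The article's hypothesis for format is non-inferiority, while its power section names equivalence. A one-sided 0.05 non-inferiority test with 220 has unadjusted power 0.94 with complete data and 0.88 at 20% missing. At one-sided 0.025 these are 0.89 and 0.81.

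**The case against.** The strongest counter-argument concerns attrition. A reader might infer from the feasibility trial that 39% of outcomes will be lost and that power will fall to 0.77 and 0.60. The article does not support that. The 39% is a dropout rate in 39 clients treated online only, and it is reported beside both ITT and completer effects. In the present trial, German participants who stop treatment are paid to continue assessments, and the dropout policy separates treatment dropout from research dropout and loss to follow-up. So 39% is only an extreme upper scenario.

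The simple figures are also pessimistic. The BSL-I is measured at 0, 3, 6, 9 and 12 months, and a mixed model uses the earlier visits. At r = 0.5, power at 20% missing is 0.95 for treatment and 0.90 for format. This stands, with two limits. The article claims no such gain, and its 230 reproduces without it. And if baseline enters the model as an unconstrained outcome, the contrast is a change score with variance factor 2(1 − r), which is 1 at r = 0.5: no gain.

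It is also fair that the format shortfall with complete data (0.88) comes from 220 against 230 and from the equivalence test, not from attrition, and that it depends on an unstated alpha and test.

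Finally, the quotas sum to 260 and recruitment runs in two cohorts of 130, so filling closed groups by site and cohort may be the real reason for the target. That is plausible, but the Power analysis section gives a different reason. Assumptions about attrition may sit in a fuller document. Their absence here is not the point; the reason and power figure that the article does state are.

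**Conclusion.** The point holds in limited form. The 230 is a complete-outcome N, and groups of 10 do not turn it into 260. For the treatment comparison the consequence is modest: 260 holds 0.90 up to about 11.5% missing unadjusted, and up to 30% missing with baseline adjustment at r = 0.5. For the format comparison the stated 0.90 is not met on the article's own inputs. Only 220 are randomised against a stated need of 230, and unadjusted equivalence power is 0.88 with complete data and 0.77 at 20% missing. A gain from baseline adjustment, or a one-sided 0.05 non-inferiority test, could close most or all of that gap, but the article states neither as the basis of its figure.

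A reader might go further and call the trial underpowered for its primary aim, or the target of 260 wrong. The documents support neither. The 30 extra patients are a real though unlabelled cushion, and 260 may be sound for logistic reasons.

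The size rests on the assumed alpha levels, 1:1 allocation, r = 0.5 where used, and no clustering within skills groups; clustering would lower all the figures.

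**What to change.** Enrolment stays as it is. Two changes to the Power analysis section:

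1. Replace the sentence that derives 260 from groups of 10 by the true reason, for example site and cohort quotas if that is the case. If the 30 extra patients are meant as an allowance for missing outcomes, say so and give the rate they cover (11.5%).
2. State power separately for the treatment comparison (N = 260) and the format comparison (N = 220). For each, name the test and alpha, and give power over a range of missing 12-month BSL-I, such as 10% to 30% with 39% as an extreme case, with the assumed baseline correlation. For format, say whether the test is equivalence or non-inferiority.

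The cost is a few sentences and a small table. The stated power becomes less favourable for the format comparison unless a justified baseline correlation is used.
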